**8.3 Secondary outcomes**

The methodology for assessing the efficacy of the intervention on elderly patients with sarcopenia is comprehensive and multi-faceted, involving the following measures:

- Body Composition Analysis: Utilizing the DBA-510 Body Composition Analyzer, participants' body weight, body water, fat mass, fat percentage, lean body weight, BMI, and segmental muscle mass of the trunk, upper, and lower limbs will be evaluated through bioelectrical impedance analysis.
- Handgrip Strength Measurement: The JAMAR electronic grip strength meter will be employed to gauge upper limb muscle strength. Participants will perform the test standing, with arms at their sides, elbows bent at 90°, and forearms supinated, exerting maximum grip strength. The highest value from four measurements (two per side) will be recorded.
- 6-Meter Walk Test: This test assesses muscle performance by having participants walk 6 meters at their usual pace. The walking speed is calculated based on the time taken to complete the distance. The test is conducted twice, and the average time and speed are noted.
- Cognitive Function Assessment: The 30-item Montreal Cognitive Assessment (MoCA, Changsha version) will be used to measure global cognitive function. This instrument is tailored for Chinese populations and scores cognitive function across multiple domains on a scale from 0 to 30, with higher scores indicating better cognitive function.
- Incidence of Falls Tracking: Participants will maintain a "fall calendar" diary to document any falls and related medical consultations monthly. This includes accidental landings on the floor or ground or collisions with objects. The collection of fall data commences with the first intervention class and continues until the intervention's conclusion or until a participant's withdrawal, death, or loss to follow-up.

1. **Quality control**

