**10.1 Power calculation**

The prevalence of falls and fractures due to the diminution of muscular mass and function underscores the clinical urgency and grave repercussions associated with sarcopenia. Drawing upon empirical evidence from a preceding trial targeting older adults predisposed to falls ^[14]^, the Short Physical Performance Battery (SPPB) is employed as the primary efficacy index. Utilizing a two-sided test with a power of 90% and a significance level of 5%, the requisite sample size for a single intervention group is deduced to be approximately 36. Accounting for an anticipated dropout rate of 20%, each group necessitates 45 participants diagnosed with sarcopenia.

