**10.2 Data analyses**

Following an intention-to-treat (ITT) protocol, those whose cumulative time of exercise reaches 80% of the amount to be completed and not higher than 120% of that will be classified into per protocol set (PPS). Categorical variables will be presented as percentages or frequencies. As for continuous variables, normally distributed data will be described by mean ± standard deviation, while non-normally distributed data will be described using median [interquartile range (IQR)]. Baseline demographic descriptors and outcome measures wil be compared across groups by using analysis of variance for continuous variables and the $\chi$*^2^* (or Fisher exact) test for categorical variables. Within the scope of this investigation, the Generalized Estimating Equations (GEE) framework was employed to evaluate the impact of Baduanjin exercise on sarcopenia among the elderly cohort. GEE is a robust statistical approach designed to analyze correlated data or repeated measurements over time, rendering it particularly adept at accommodating incomplete datasets and multiple observational instances.Initially, an exhaustive data cleansing and encoding procedure will be undertaken to ascertain the precision and integrity of the dataset. Continuous variables will undergo a distributional analysis to discern the necessity of transformation to align with the normal distribution assumption. Categorical variables will be delineated through frequencies and percentages.The GEE model will incorporate temporal factors as a repeated measures variable, alongside other pertinent covariates that may influence the outcomes, such as age, gender, and baseline muscle mass index. The inclusion of interaction terms pertinent to time will facilitate an in-depth assessment of the longitudinal effects of Baduanjin exercise on sarcopenia. The model’s fit will be gauged using the Quasi-likelihood under the Independence model Criterion (QIC), with preference given to the model demonstrating the minimal QIC value. Additionally, a thorough examination of model residuals will be conducted to validate the adherence to underlying assumptions.Two-sided P values of less than 0.05 will be considered statistically significant. Analyses will be conducted using SPSS version 23.0 (IBM Corp) or GraphPad Prism version 7.0 (GraphPad Software).

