**Table 2. Schedule of trial procedures**

| **Period** | **Screening** | **Intervention period** | | |
| --- | --- | --- | --- | --- |
| **Time point** | **0 wk** | **0 wk** | **12 wk** | **24 wk** |
| **Enrollment** | **×** |  |  |  |
| Eligibility screening | **×** |  |  |  |
| Informed consent |  | **×** |  |  |
| **Allocation** |  |  |  |  |
| **Intervention** |  |  |  |  |
| Non-sarcopenia control |  | **×** |  |  |
| Baduanjin exercise |  | **×** | **×** | **×** |
| Resistance training |  | **×** | **×** | **×** |
| **Assessments** |  |  |  |  |
| Physical function |  | **×** | **×** | **×** |
| Body composition |  | **×** | **×** | **×** |
| Handgrip strength |  | **×** | **×** | **×** |
| 6 m walking test |  | **×** | **×** | **×** |
| Cognitive function |  | **×** | **×** | **×** |
| Incidence of falls |  | **×** |  | **×** |

1. **References**
2. Morley JE. Sarcopenia:diagnosis and treatment[J]. *J Nutr Health Aging,* 2008, 12: 452-456.
5. Cao Li MD, JE. Morley MB. Sacropenia is recognized as an independent Condition by an International Classification of Disease, Tenth Revision, Clinical Modification(ICD-10) Code[J]. 2016, (17): 675-677.
6. Murton AJ. Muscle protein turnover in the elderly and its potential contribution to the development of sarcopenia[J]. *Proc Nutr Soc*, 2015:74(4): 387-396.
7. Yuwei Lin, Guiyu Qian, Meizhi Xu. Causes and effects of sarcopenia in the elderly[J].*Tertiary sports*, 2010.10, (110): 85-91.

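### Thirteen secondary efficacy measures fall under one unadjusted two-sided P<0.05 rule, with no order, gate or exploratory label, so a secondary result can be declared significant at full alpha even if SPPB is null

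*Combined protocol and SAP*

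**What the plan says.** Section 10.1 names one primary outcome: "the Short Physical Performance Battery (SPPB) is employed as the primary efficacy index". The sample size in sections 4 and 10.1 is built on it alone.

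Section 8.3 introduces the secondary outcomes as efficacy measures: "The methodology for assessing the efficacy of the intervention on elderly patients with sarcopenia is comprehensive and multi-faceted, involving the following measures". The list contains:

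- body composition, with nine variables: "body weight, body water, fat mass, fat percentage, lean body weight, BMI, and segmental muscle mass of the trunk, upper, and lower limbs";
- handgrip strength, one value per participant: "The highest value from four measurements (two per side) will be recorded";
- the 6-metre walk: "The test is conducted twice, and the average time and speed are noted" (over a fixed distance, time and speed carry the same information, so this counts as one measure);
- the MoCA, which "will be used to measure global cognitive function";
- falls, from a diary.

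Table 2 schedules body composition, handgrip, the 6-metre walk and cognition at baseline, week 12 and week 24. Falls are marked at baseline and week 24.

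Section 10.2 describes a GEE model with time and time-interaction terms. It also names analysis of variance and chi-square (or Fisher) tests for comparing outcome measures between groups. It closes with the only significance rule in the plan: "Two-sided P values of less than 0.05 will be considered statistically significant". The rule is not restricted to the primary outcome. The supplied text has no multiplicity adjustment, no order among the secondaries, no condition that SPPB be significant first, and no statement that secondary results are exploratory.

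**The concern.** Naming SPPB as the sole primary outcome protects the SPPB test. It does not restrain what may be said about the other outcomes. Under the rule as written, any secondary measure with P<0.05 counts as statistically significant, whatever SPPB shows, and section 8.3 has already called these measures of efficacy.

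That matters most if SPPB is null. The comparator is an active resistance programme of the same length and frequency, so a null primary result is a realistic possibility. Section 2 says the trial is meant to support wide uptake of Baduanjin. A chance finding on, say, trunk muscle mass or the MoCA could then be presented as a demonstrated benefit, and the plan contains no rule against it.

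**Working it through.** **Count.** Nine body-composition variables + handgrip + 6-metre walk + MoCA + falls = 9 + 1 + 1 + 1 + 1 = 13 measures (section 8.3). Twelve of these have two post-baseline visits and falls has one (Table 2): 12 × 2 + 1 = 25 measure-visit pairs. If body composition is treated as one outcome, there are 5.

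**Plan's own figure.** The documents state no familywise error rate for the secondaries, so there is none to reproduce. The only input taken from the plan is the per-test threshold, two-sided 0.05 (section 10.2).

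**Independent tests.** If the arms do not differ on any measure, P(at least one P<0.05) = 1 − 0.95^k:

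- k = 5: 1 − 0.95^5 = 0.226
- k = 13: 1 − 0.95^13 = 0.487
- k = 25: 1 − 0.95^25 = 0.723

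Counting only results that favour Baduanjin, each test has probability 0.025, so 1 − 0.975^k gives 0.280 for k = 13 and 0.469 for k = 25.

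**Correlated tests.** The measures are clearly related: BMI is weight over squared height, and fat and lean mass make up weight. For test statistics with common correlation r, write each as √r·U + √(1−r)·E, with U and E independent standard normal. The chance that all k stay within ±1.96 is the average over U of [Φ((1.96 − √r·U)/√(1−r)) − Φ((−1.96 − √r·U)/√(1−r))]^k, and one minus this is the familywise rate. For results favouring Baduanjin only, the second Φ term is dropped. Numerical integration gives:

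| Tests | Direction | r = 0 | r = 0.5 | r = 0.9 |
|---|---|---|---|---|
| 5 (body composition as one) | either | 23% | 18% | 10% |
| 13 (one test per measure) | either | 49% | 33% | 14% |
| 25 (every measure-visit pair) | either | 72% | 47% | 16% |
| 13 | favours Baduanjin | 28% | 17% | 7% |
| 25 | favours Baduanjin | 47% | 23% | 8% |

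**A more structured assumption.** With correlation 0.8 within body composition, 0.3 between all other pairs and 0.7 between the two visits, simulation gives 30% for 13 tests and 43% for 25. In favour of Baduanjin only, it gives 15% and 22%.

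The documents give no correlations, so every value of r here is an assumption. The lowest either-direction figure, 5 tests at r = 0.9, is 10%, twice the per-test 5%. The lowest Baduanjin-only figure in the table, 7%, compares with 2.5% for a single test in one direction.

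**The case against.** The strongest reply is that the plan does have a hierarchy where it matters. SPPB is the sole primary outcome and the only one powered, everything else sits under a heading that says secondary, and leaving labelled secondaries unadjusted is a common reporting choice. The plan promises no familywise rate for them: the 0.05 in section 10.2 is a per-test threshold, and the 5% in section 10.1 belongs to the SPPB sample size. All of this stands. A reader might infer that the error rate of the primary test is inflated by the secondaries; the documents do not support that.

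The count can also be challenged. Table 2 schedules measurements, not tests. A GEE with time interactions could yield one test per measure, so 25 is an upper bound and not the written plan. Body composition is one bullet in section 8.3 and one row in Table 2, and on that reading there are five outcomes. Both points stand, and the table above therefore shows 5, 13 and 25 side by side. In the other direction, section 10.2 names a second testing route beside GEE and a per-protocol set beside intention-to-treat, and neither is counted here.

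Finally, the either-direction figures include chance results favouring resistance training. The feared misuse is a false Baduanjin benefit, for which the lower rows of the table are the relevant ones.

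None of these points supplies the missing statement. A label of secondary does not say whether P<0.05 on such an outcome may be claimed as significant efficacy, and the rule as written says that it may be called significant.

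**Conclusion.** The point holds as a gap in the secondary family only. Secondary measures presented as evidence of efficacy may be declared significant at full alpha regardless of SPPB. If the arms do not differ, the chance of at least one such result with one test per measure is about one in three at an assumed correlation of 0.5 (14% to 49% over correlations 0.9 to 0). It is about one in six in favour of Baduanjin (7% to 28%). The 5-test and 25-test counts bracket the either-direction figure at 18% and 47% for the same correlation.

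A reader might infer that a false-positive secondary finding is more likely than not. That is too strong: the rate passes 50% only if all 25 pairs are tested and correlations are low to moderate, and a chance result in favour of Baduanjin stays below 50% even with 25 independent tests. It is a worthwhile, inexpensive correction and not a flaw in the primary analysis.

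**What to change.** In section 10.2, limit the P<0.05 significance statement to the primary SPPB comparison. Add that all secondary outcomes, including their week-12 comparisons, are exploratory and will be reported as between-group estimates with 95% confidence intervals, with no claim of statistical significance or proven efficacy. In section 8.3, describe these outcomes as supportive measures instead of measures for assessing efficacy.

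If the sponsor wants a confirmatory claim on a few week-24 secondaries, a fixed test order gated on SPPB would allow it. That is optional, and the choice of outcomes and order is the sponsor's. The gate would also require section 10.2 to name the SPPB visit and contrast that open it, which it does not do at present.

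The cost is a few sentences, with no extra participants or data. The downside is that secondary results can no longer be called statistically significant, except any placed in such an order.

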**Table 2. Schedule of trial procedures**

| **Period** | **Screening** | **Intervention period** | | |
| --- | --- | --- | --- | --- |
| **Time point** | **0 wk** | **0 wk** | **12 wk** | **24 wk** |
| **Enrollment** | **×** |  |  |  |
| Eligibility screening | **×** |  |  |  |
| Informed consent |  | **×** |  |  |
| **Allocation** |  |  |  |  |
| **Intervention** |  |  |  |  |
| Non-sarcopenia control |  | **×** |  |  |
| Baduanjin exercise |  | **×** | **×** | **×** |
| Resistance training |  | **×** | **×** | **×** |
| **Assessments** |  |  |  |  |
| Physical function |  | **×** | **×** | **×** |
| Body composition |  | **×** | **×** | **×** |
| Handgrip strength |  | **×** | **×** | **×** |
| 6 m walking test |  | **×** | **×** | **×** |
| Cognitive function |  | **×** | **×** | **×** |
| Incidence of falls |  | **×** |  | **×** |

1. **References**
2. Morley JE. Sarcopenia:diagnosis and treatment[J]. *J Nutr Health Aging,* 2008, 12: 452-456.
5. Cao Li MD, JE. Morley MB. Sacropenia is recognized as an independent Condition by an International Classification of Disease, Tenth Revision, Clinical Modification(ICD-10) Code[J]. 2016, (17): 675-677.
6. Murton AJ. Muscle protein turnover in the elderly and its potential contribution to the development of sarcopenia[J]. *Proc Nutr Soc*, 2015:74(4): 387-396.
7. Yuwei Lin, Guiyu Qian, Meizhi Xu. Causes and effects of sarcopenia in the elderly[J].*Tertiary sports*, 2010.10, (110): 85-91.
